### Adverse events

Wearing accelerometers and completing questionnaires pose little risk of harm to participants. Teaching strategies were based on theory and research evidence, indicating that they can effectively motivate behavior and no adverse events were reported.

### Planned statistical analysis

To assess the reliability of the teacher behavior ratings provided by the independent observers, intra-class correlation coefficients (ICCs) will be calculated. The fidelity of the interventions will be assessed using a MANOVA (with follow-up comparisons). If the manipulation of teacher strategies was successful, independent observer ratings of the intended strategy for each condition should be higher than ratings in other conditions. For example, ratings of choice should be higher in the two choice conditions than in any of the relevance and control conditions. To assess differences in primary and secondary outcome variables, linear mixed model analyses will be run on accelerometer counts, motivation and basic needs satisfaction, with students nested within teachers as a random effect. All analyses will be conducted based on the intention-to-treat principle.

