**Methods/design:**

This study employed a cluster-randomized controlled trial design. Following a familiarization session, PA levels and hypothesized PA antecedents were measured during a baseline lesson and a post-intervention or control lesson. Teachers (n = 16) and their classes from five secondary schools in Sydney, Australia were randomly assigned into four blocks and instructed to provide one of four 20-min lesson teaching strategy conditions: (1) explaining the relevance of activities; (2) providing choice from PA options selected by the teacher; (3) providing equipment and free choice of activities; or (4) usual practice. The primary outcomes were lesson time spent in moderate-to-vigorous PA, and motivation towards the lesson. Secondary outcomes were perceptions of teacher behavior, psychological needs satisfaction, and lesson time spent in sedentary behavior. PA and sedentary behavior were measured during baseline and post-intervention lessons with waist-mounted Actigraph GT3X accelerometers. Teacher behavior, psychological needs satisfaction, and motivation were assessed via questionnaires at the end of each lesson. Linear mixed-model analyses will be run on all outcomes, with students nested within teachers as a random effect.

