### Hypotheses

Compared with usual practice, we hypothesized that PE lessons in which teachers explained the relevance of activities and provided students with choices would:

1. show greater increase in the percentage of time students spend in moderate-to-vigorous physical activity during PE lessons.

2. show greater decrease in the percentage of PE lesson time that students spend in sedentary behavior.

3. show greater increase in students’ autonomous motivation during lessons.

4. show greater decrease in students’ controlled motivation during lessons.

5. show greater increase in students’ perceptions of autonomy, competence, and relatedness during lessons.

6. show greater increase in students’ and independent raters’ perceptions of teachers’ autonomy supportive behavior.

7. produce effects that would be by teachers’ autonomy supportive behavior and students’ needs satisfaction and motivation (see Figure 1).

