### Outcome measures

Different schools and classes were expected to have PE lessons of varying duration and, due to fatigue, it is possible that MVPA levels at the end of longer lessons could be lower than earlier in the lesson. To standardize across lessons of varying durations, all PA data collection occurred during the first 20 min of teaching time during each lesson for the baseline and post-intervention assessments (i.e., after students had changed their clothes and been fitted with an accelerometer). ActiGraph GT3X accelerometers (ActiGraph; Pensacola, FL) were used to assess PA levels (percentage of time spent in MVPA and percentage of time spent sedentary) of each student in this study. Monitors were synchronized with an external clock and initialized to start recording data in three axes of motion in 1-sec epochs, a minimum of 30 min before and after the scheduled PE lessons. Research assistants helped students place an Actigraph monitor, via adjustable elastic belt, over the right iliac crest, prior to the start of each observed PE lesson, to wear for the duration of lesson. Raw accelerometer counts were uploaded to a lab computer, and saved to a customized Microsoft Excel file. Data outside the recorded start and finish time for given sessions was disregarded. Data were checked for spurious values that did not coincide with the direct observation records; all data between start and finish times for all lessons were included in the analyses. Freedson’s MET prediction equation [38] was used to determine PA intensity, and 100 counts per minute was used as a criterion to determine sedentary time [39].

At the 20-min mark of the baseline and post-intervention lessons, each student completed the four items from the Teacher as Social Context Questionnaire described previously. This version of the questionnaire is designed to measure students’ perceptions of their teachers’ autonomy supportive behavior [21] (e.g., “The teacher gives us choices about how we do the things in today’s class”). Students also completed measures of autonomy need satisfaction [24,40], competence need satisfaction [41], relatedness need satisfaction [42], and controlled and autonomous forms of motivation (Situational Motivation Scale) [43]. Each measure has received empirical support regarding reliability and validity in English-speaking samples of this age group [11,14,21,41-44].

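### The analysis section names accelerometer counts as the modelled physical activity variable, contradicting the MVPA and sedentary-time outcomes set elsewhere in the protocol

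*Protocol article*

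**What the plan says.** All references are to the protocol article.

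- **Abstract, Methods/design:** "The primary outcomes were lesson time spent in moderate-to-vigorous PA, and motivation towards the lesson". Sedentary lesson time is listed among the secondary outcomes. The abstract then states: "Linear mixed-model analyses will be run on all outcomes, with students nested within teachers as a random effect".
- **Aims of the study:** Research Question 1 marks MVPA as primary and sedentary behavior as secondary.
- **Hypotheses:** hypothesis 1 is that the strategies will "show greater increase in the percentage of time students spend in moderate-to-vigorous physical activity during PE lessons". Hypothesis 2 is that they will "show greater decrease in the percentage of PE lesson time that students spend in sedentary behavior".
- **Outcome measures:** the accelerometers serve to assess "percentage of time spent in MVPA and percentage of time spent sedentary" over the first 20 minutes of teaching. Raw counts are what is uploaded from the device. After that, a "MET prediction equation [38] was used to determine PA intensity, and 100 counts per minute was used as a criterion to determine sedentary time".
- **Planned statistical analysis:** the sentence opens "To assess differences in primary and secondary outcome variables" and continues that "linear mixed model analyses will be run on accelerometer counts, motivation and basic needs satisfaction".

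**The concern.** The article uses counts for the raw device signal and percentages of time for the outcomes. The analysis sentence names the signal. A mean or total count reflects the volume of movement. Percentage MVPA and percentage sedentary reflect how much of the lesson lies above one cut-point or below another.

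Read literally, the sentence attaches no model to the scale on which hypotheses 1 and 2 are written. It also leaves two candidate variables for a primary outcome. That matters because data collection is described in the past tense and the analysis in the future tense, so the choice could be made after the data are in hand. The choice could also bear on how the arms compare: the Intervention and fidelity check section supports the free-choice arm with earlier evidence on total activity accumulated, which is closer to counts than to time above a threshold.

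A lesser point is that the list of modelled variables leaves out students' perceptions of teacher behaviour, a secondary outcome.

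**Working it through.** **1. The statements side by side**

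| Section | Physical activity variable | Scale |
|---|---|---|
| Abstract | MVPA (primary), sedentary (secondary) | lesson time |
| Aims of the study | MVPA (primary), sedentary (secondary) | not given |
| Hypotheses 1 and 2 | MVPA, sedentary | percentage of time |
| Outcome measures | MVPA, sedentary | percentage of time, derived from counts |
| Planned statistical analysis | accelerometer counts | counts |

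Time and percentage do not conflict with each other. In a fixed 20-min segment, minutes in MVPA = 20 × proportion in MVPA. Only the last row is out of line.

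**2. Are counts a stand-in for the percentages?**

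The following values are assumed for illustration and are not in the documents. Let T be the count level that marks MVPA. The segment has 20 × 60 = 1,200 one-second epochs. Mean count = Σ (share of epochs × level).

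- Student A, 40% of epochs at 1.2T and 60% at 0.1T: 0.40 × 1.2T + 0.60 × 0.1T = 0.48T + 0.06T = 0.54T. MVPA is 40%.
- Student B, 25% at 2.5T and 75% at 0.1T: 0.25 × 2.5T + 0.75 × 0.1T = 0.625T + 0.075T = 0.70T. MVPA is 25%.

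A ranks higher on MVPA and B ranks higher on counts.

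Now hold MVPA at 25%, keep the other 75% at 0.1T, and vary the active intensity:

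| Active intensity | Mean count | MVPA |
|---|---|---|
| 1.5T | 0.375T + 0.075T = 0.45T | 25% |
| 2T | 0.50T + 0.075T = 0.575T | 25% |
| 2.5T | 0.625T + 0.075T = 0.70T | 25% |
| 3T | 0.75T + 0.075T = 0.825T | 25% |

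Mean counts can change while the primary outcome stays the same. A single count summary also cannot determine two separate percentages, so it cannot serve both hypothesis 1 and hypothesis 2.

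**3. Does the sample size depend on this?**

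Inputs from Sample size and power calculation: f = 0.25, r = 0.5, alpha .05, power 95%, cluster size 25, intra-class correlation 0.1. The design has four groups and two measurements.

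- Within-between interaction, noncentral F: λ = f² × N × 2/(1 − r). At N = 76, λ = 0.0625 × 76 × 2/0.5 = 19.0 on 3 and 72 degrees of freedom, and power is 0.959. The smallest sufficient N is 73, which becomes 76 for four equal groups. This matches the stated 76.
- Design effect: 1 + (25 − 1) × 0.1 = 3.4, and 76 × 3.4 = 258.4 (stated 258).
- Increase of 20%: 258 × 1.2 = 309.6 (stated 308, a difference of 1.6 students).

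The calculation uses a standardised f and does not refer to counts or percentages. Settling the dependent variable leaves these figures as they are.

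**The case against.** A reader might infer that the planned model does not test the primary outcome, or that no model at all addresses hypotheses 1 and 2. The documents do not support going that far, for three reasons.

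1. There are two primary outcomes, and the other one, motivation, is named in the model.
2. The abstract lists MVPA and sedentary lesson time as outcomes and assigns mixed models to all outcomes.
3. The analysis sentence itself opens by saying that the models assess the primary and secondary outcomes. No section defines mean or total counts as an outcome, so counts may be shorthand for the variables derived from them. On that reading, sedentary time is covered too.

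It is also fair to say that four other sections fix MVPA as the activity outcome, so reporting counts as primary would visibly depart from them. The missing student perceptions can be put down to a shortened list that the abstract covers.

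These arguments limit the finding but do not remove it. The shorthand reading has to be inferred against the article's own use of the word, because Outcome measures keeps raw counts distinct from what is derived from them. Nor is this a detail left to a fuller document: the article does name a dependent variable, and the name conflicts with its outcome definition.

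**Conclusion.** The contradiction stands. The analysis section names a different physical activity variable from the one in the outcomes and hypotheses, and it concerns one of the two primary outcomes. The statement that hypotheses 1 and 2 go untested holds only on a literal reading of one phrase; the abstract's commitment to all outcomes suggests that the percentages may be intended.

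No effect on the trial's result can be sized from the documents. The numerical examples rest on assumed intensities. They show that counts and percentage MVPA can rank students differently, and a reader should not infer from them how far comparisons between arms would diverge. The sample size is unaffected. The omission of students' perceptions of teacher behaviour is minor.

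**What to change.** In Planned statistical analysis, replace accelerometer counts with *percentage of the 20-min lesson segment in MVPA (primary) and percentage sedentary (secondary)*. If counts are to be analysed as well, label that analysis supplementary. For consistency with the abstract, add students' perceptions of teacher behaviour to the list of modelled outcomes.

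The cost is one sentence of text. Both percentages are already derived under Outcome measures, so no new data, processing or sample size work is needed.

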## Methods/design

The Human Research Ethics Committee at the University of Western Sydney provided ethical approval for this cluster-randomized controlled trial. The study was conducted in Independent and Catholic schools in Sydney, New South Wales, Australia during 2011. Ten schools were identified using publicly available listings, and invited via telephone and email through publicly available contact details. The first five schools whose principal provided consent were included in the study. Once consent was also received from department heads and teachers of Year 8 PE classes, the research team met briefly with the students to provide basic information about the study. At this time, information sheets and consent forms were distributed to students. Students who were unable to participate in PE classes were not eligible to participate in the study. All other Year 8 PE students who returned signed parental consent forms and provided personal assent were allowed to participate in the study. Students who did not return consent forms still participated in the lessons alongside their peers, but did not wear accelerometers, or complete questionnaires.

Figure 2 provides a summary of the study design, a cluster-randomized controlled trial with four study arms. To begin, a familiarization session was held during a PE lesson. During this lesson, students wore an accelerometer and teachers wore a microphone attached to their shirt that connected wirelessly to an audio recording device. The purpose of this session was to minimize potential reactivity to these monitoring devices during baseline and post-intervention sessions. Data collected during this familiarization lesson will not be analyzed. Baseline and post-intervention data were collected from all participating students, regardless of study arm, during and immediately after two 20-min segments of PE lessons. In between these two lessons, teachers received a brief intervention (three experimental arms) or were asked to continue with usual practice (control arm).

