### Sample size and power calculation

Lonsdale et al. [11] found a large difference in PA levels between free choice and structured PE lesson conditions (Cohen’s *d* = 1.07). We adopted a conservative approach and estimated a moderate effect size (medium *f* = 0.25) for mixed (between and within-subjects) analysis. Based on this estimation, as well as an estimated correlation of *r* = 0.5 among the repeated measures of PA (*r* = .53 in a previous study [11]), we required a sample of 76 students in order to achieve 95% power, with alpha set at .05. Taking into account the clustered nature of the data, this sample size was multiplied by a correction factor of 1+(*m* - 1)ρ, called the design effect, where *m* is the average cluster size and ρ is the intra-class correlation coefficient [35]. Assuming an *m* of 25 students per class and ρ = 0.1 (estimated based on a previous study [36]), the correction factor is 3.4. As a result, a sample of 258 students (i.e., 76 × 3.4 = 258) was required. To allow for lack of informed parental consent or assent from some students, and to protect against participant attrition across the four teaching conditions, we attempted to increase the sample by 20% and recruit 308 students from 16 PE classes.

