### Randomization

The 16 PE teachers, with their students, were randomly assigned to one of four conditions (three interventions and one control). An independent researcher, blinded to the study hypotheses, performed the allocation after the baseline assessment was administered. Randomization was conducted at the class-level and within schools to control for school characteristics, using a computerized random number generator with blocked randomization scheme (block size = 4). School 1 (Catholic – coeducational), School 2 (Independent – girls only), and School 3 (Independent – coeducational) each provided four classes of students and one class from each school was randomly assigned to one of the four conditions. School 4 and School 5 (two classes each) were both Catholic boys schools. Together, these two schools constituted the final block from which four classes were randomly assigned.

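### On its natural reading, the stated random effect leaves class-wide shifts between the two lessons out of the error for arm differences in change, so false positives can exceed 5%

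*Protocol article*

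**What the plan says.** Planned statistical analysis (and the Abstract, in the same words) describes linear mixed models "with students nested within teachers as a random effect". It does not write out a time or arm-by-time term, how baseline enters, or a degrees-of-freedom method.

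Other sections fix the setting:
- **Randomization:** "Randomization was conducted at the class-level and within schools to control for school characteristics". There are 16 classes, four per arm, in four blocks.
- **Methods/design:** data were collected "during and immediately after two 20-min segments of PE lessons", one at baseline and one after the intervention.
- **Hypotheses:** the first is that the strategy lessons would "show greater increase in the percentage of time students spend in moderate-to-vigorous physical activity during PE lessons", compared with usual practice. The other outcome hypotheses are also about increases or decreases.
- **Sample size and power calculation:** for an analysis that is both between and within subjects, "we required a sample of 76 students in order to achieve 95% power, with alpha set at .05". The section continues: "Taking into account the clustered nature of the data, this sample size was multiplied by a correction factor of" 1 + (m − 1)ρ, with m = 25 and ρ = 0.1, which gives 3.4.

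**The concern.** A student can be a separate level of random effect only if that student contributes more than one observation. Here the repeated observations are the two lessons. Together with hypotheses about greater change and a power calculation for a between-and-within test, this points to an arm-by-time contrast with a random intercept for teacher and one for student within teacher.

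That model protects a comparison of levels against clustering, but not a comparison of changes. Each class is observed in one lesson per time point. If the activity, the space or the day shifts the whole class, the shift has no term in the model and goes into the residual as if each student had moved independently. Classes were randomised, so this class-wide shift is exactly the variation against which the strategies should be judged.

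At stake is the validity of the arm comparisons: standard errors would be too small, and ordinary lesson-to-lesson variation between classes could be reported as a strategy effect.

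**Working it through.** **1. The plan's own sample size.** For the between-and-within interaction, the noncentrality is λ = f²·N·k/(1 − r). With f = 0.25, k = 2 lessons and r = 0.5, λ = 0.0625 × 2/0.5 × N = 0.25N. On 3 and N − 4 degrees of freedom, N = 73 gives 95.1% power. Rounded up to equal arms, N = 76 gives 95.9%. The design effect is 1 + 24 × 0.1 = 3.4, and 76 × 3.4 = 258.4. Adding 20% to 258 gives 309.6, against the stated 308. The arithmetic reproduces and is not in question. Students per class are 258/16 = 16.1 to 308/16 = 19.25.

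**2. What the intercepts do.** For student i in class j, write the baseline and post values as Y₀ = T_j + S_ij + e₀ and Y₁ = T_j + S_ij + arm effect + e₁. The change is the arm effect + (e₁ − e₀), because T_j and S_ij drop out. With balanced data the arm-by-time test is therefore the student-level analysis of change scores on N − 4 degrees of freedom, which is 252 for 16 × 16 = 256 students. The between-class degrees of freedom are 16 − 4 = 12. As a check, 1,643 full mixed-model fits (16 per class, correlation of change 0.1, no true effect) rejected in 37.2%. The change-score analysis of the same data rejected in 36.4%.

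**3. False positives at nominal 5%.** The results come from 40,000 simulated trials per setting, with 4 arms × 4 classes and no true effect. The within-class correlation of change is an assumption, shown as a range.

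| Correlation of change | Four-arm test, 16 per class | Four-arm test, 19 per class | One strategy vs control, 16 | One strategy vs control, 19 |
|---|---|---|---|---|
| 0 | 5.2% | 4.9% | 4.9% | 5.1% |
| 0.01 | 7.9% | 8.7% | 6.9% | 7.1% |
| 0.02 | 10.9% | 12.5% | 8.6% | 9.4% |
| 0.04 | 17.8% | 20.9% | 11.8% | 13.7% |
| 0.1 | 38.0% | 43.4% | 21.8% | 24.8% |
| 0.2 | 60.0% | 65.4% | 34.0% | 37.0% |

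A class-level F test on 3 and 12 degrees of freedom stayed between 4.7% and 5.2% in every setting.

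A hand check for one comparison at 0.1: the variance of an arm mean change is too small by 1 + 15 × 0.1 = 2.5 (16 per class) or 1 + 18 × 0.1 = 2.8 (19 per class). The effective critical values are 1.96/√2.5 = 1.24 and 1.96/√2.8 = 1.17, with two-sided tail areas of about 21.5% and 24%.

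**4. Which correlation applies.** The sample size section multiplies the N of the between-and-within test by a factor using ρ = 0.1, which amounts to a correlation of about 0.1 for change. If ρ is instead the correlation within one lesson, set the total variance to 1 at each lesson and r = 0.5. The variance of change is then 2(1 − 0.5) = 1, and its class part is 2 × 0.1 × (1 − c), where c is the correlation of the class effect between the two lessons. The correlation of change is 0.2(1 − c): 0 at c = 1, 0.02 at c = 0.9, 0.04 at c = 0.8, 0.1 at c = 0.5 and 0.2 at c = 0.

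**5. Power with the class as the unit of error.** With the plan's design effect, λ = 0.25 × 258/3.4 = 18.97. On 3 and 12 degrees of freedom, power is 89%. With the smaller analysed classes and a correlation of change of 0.1, it is 96% (N = 258) or 97% (N = 308).

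**The case against.** The strongest reply is that the article gives one condensed clause. A reader might infer that the model has random intercepts and nothing else, but the text says neither, and a fuller plan could contain a teacher-by-time effect. Students nested in teachers is also common shorthand for a two-level hierarchy. A post-lesson model adjusted for baseline with a random teacher effect would keep the clustering. The research questions ask only whether students differ across conditions. This stands as a limit on certainty: the intercept-only model is inferred. It does not remove the point, because the random structure is the one model feature the article chose to state, and the reading that fits the hypotheses and the power calculation is the one that loses the clustering.

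A reader might also conclude that false positives are far above 5% whatever the data. The documents do not support that. The article does not call ρ = 0.1 a correlation of change. If class effects were identical in both lessons there would be no inflation. Teachers were asked to keep the second lesson close in structure to the first, and measurement was confined to the first 20 minutes. Both would tend to reduce class-by-lesson variation, but they do not remove it.

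Nor can the percentages be carried over to every outcome: no within-class correlation is given for motivation, needs satisfaction or perceived teacher behaviour.

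Finally, the 5% result was simulated for a class-level F test, not for the mixed models proposed below. With equal class sizes and a positive class-by-lesson variance estimate, the teacher-by-time model leads to that same test. With unequal classes the agreement is approximate.

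**Conclusion.** The concern holds in conditional form. If the sentence is followed on its natural reading, the arm-by-time test ignores the class randomisation that the sample size section pays for with a factor of 3.4. At the plan's ρ, used for change as that section uses it, the nominal 5% four-arm test gives about 37–43% false positives, and a single strategy-versus-control test about 21–25%. The full range runs from no inflation to 60–65%, according to a class-level correlation of change that the article does not state. Even small values matter: 0.02 already gives 11–13%. The result assumes 16 to 19 analysed students in each of 16 classes, balanced data, and no class-by-lesson term. Because both primary outcomes rest on this model, the sentence needs to be settled before analysis.

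**What to change.** Amend the model sentence in Planned statistical analysis in one of two ways:

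- **(a)** Analyse the post-intervention value with arm, randomisation block and baseline as fixed effects and teacher as a random intercept.
- **(b)** Keep both lessons as repeated measures and add a random teacher-by-time (class-by-lesson) effect to the teacher and student intercepts.

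In either case, name Kenward-Roger or Satterthwaite degrees of freedom, so that arm effects are tested on about 12 (16 − 4), or 9 with block (16 − 4 − 3). If such a model is already intended, state it.

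The cost is one sentence and no new data. Confidence intervals will be wider, and power somewhat below the stated 95% if the plan's own design effect applies: about 89% on 12 degrees of freedom.
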